### *3.1.8. Randomization, sequence generation, allocation and concealment*

Each of the twelve food products (six CSB and six LNS) will be randomly letter coded by GC Rieber Compact by the letters M, N, P, Q, R, S, T, U, V, X, Y, Z, ( "O" is omitted due to similarity with "Q"). Two identical documents (code documents) stating which product corresponds to which code is prepared and placed in sealed envelopes also by GC Rieber Compact. The code documents are kept in safety boxes, one at the MSF-DK office, and one at the Dept. of Nutrition, Sports and Exercise, University of Copenhagen. The code will first be revealed following the primary analysis.

Stratified, blocked randomization will be used to randomly allocate children to the twelve experimental foods. Stratification will be done by recruitment site (CSPA), ie, separate random sequences will be made, one to be used at each of the five sites. This will ensure that site, which may be strongly associated with the outcome and thus an important potential confounder, will be equally distributed between the intervention groups. Blocked randomisation will be used, with varying block size, to ensure that for each site, children will

be allocated evenly to the trial arms. The random sequences (RS) are made using [www.randomization.com](http://www.randomization.com).

Sealed envelopes will be labelled with the unique patient code and will contain the intervention allocated to the patient. The envelopes will be opened only after the completion of the screening and the final recruitment of the patient, ensuring concealment.

In case two or more siblings are presenting MAM, only one child per mother will be included in the trial (i.e. the first child diagnosed with MAM or, if several siblings are diagnosed on the same day, one of them will be selected by simple random sampling). The other siblings will however benefit from the same nutritional intervention as her/his brother/sister (whether it is, the iCSBs or LNS group). For these siblings, no specific assessments would be done except the routine medical evaluation and standard anthropometric measurements.

#### *3.1.9. Blinding*

This is an open trial since participants will not be blinded with respect to main type of food (LNS or iCSBs). However, within the arms with either iCSBs or LNS, participants will be blinded to the soy and milk content of the food. The investigator measuring the primary outcome (lean body-mass using tracer dilution) will be kept unaware of the allocation group and will therefore be blinded with respect to main type of food. In addition, the investigators measuring other biological factors, physical activity and milestones development will be blinded with respect to main type of food.

After baseline data have been collected, the child will be referred to the Supplement Responsible (SR). Only the SR will have access to the random sequence list.

For further information on the randomization and management of the experimental products, please see Standard Operating Procedure in annex 6

#### *3.1.10. Participants follow-up chart*

Active screening will be done within the community and children 6-23 months presenting at the CSPA will be assessed for eligibility. The caretakers of those eligible will receive detailed information by the study staff about the trial (see information notice in annex7) and will be invited to freely consent to participate. They will be asked to sign (or thumb-print if illiterate) the informed consent form (see in annex 8). An independent literate witness (from the community) will be required to be present during the reading of the consent form and sign in addition to the fingerprint requested from a non-literate study participant. After written informed consent has been obtained, children will be assigned a sequential study number.

This number will be reported on all the participant documents as well as on an identification bracelet and an identification card (that will include a picture of the child and his/her caretaker). Furthermore participation will be registered in the patient health card, to avoid that the patient seeks nutritional supplementation or treatment from other CSPS.

The participants will be assessed as described in the following Table 2. A participant will be considered as having missed the fortnightly or monthly visit if they present with a delay of more than one week. If the patient does not show up at the centre, after more than one week he/she will be visited at home to evaluate reasons for defaulting. Defaulting due to death will be reported with morbidity data

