#### **Safety**

Adverse events (AE): Although we do not expect the foods to cause any harm, peanut, milk, and soy proteins can be allergenic. AE could include: digestive symptoms (diarrhea and/or vomiting), cutaneous symptoms (hives) and, respiratory symptoms (wheezing) within one hour after ingestion of the food. The first dose of the products will be taken under observation and anaphylactic kits will be available at each recruitment sites, where the study nurse will be trained in how to respond to any allergic reaction. All signs of possible allergic reaction will be recorded as part of the fortnightly morbidity assessment, and will be treated accordingly. Serious AE related to this study could include: angioedema, anaphylactic reaction, and death. All serious AE will be immediately communicated to the trial manager who will ensure that they are addressed in an appropriate and timely manner and reported to all study investigators and trial sites, according to Good Clinical Practice. The trial manager will be responsible for the medical management of all adverse events, and will ensure referral to the national health system if necessary, including follow-up.

---

 Definition of the ICH-GCP glossary: Adverse Event : Any untoward medical occurrence in a patient or clinical investigation subject administered a pharmaceutical product and which does not necessarily have a causal relationship with this treatment. An adverse event (AE) can therefore be any unfavorable and unintended sign (including an abnormal laboratory finding), symptom, or disease temporally associated with the use of a medicinal (investigational) product, whether or not related to the medicinal (investigational) product. Serious Adverse Event (SAE): Any untoward medical occurrence that at any dose: results in death, is life-threatening, Requires inpatient hospitalization or prolongation of existing hospitalization, results in persistent or significant disability/incapacity, or is a congenital anomaly/birth defect.

Furthermore the national ethical review board will be notified and will be asked to advise the investigators of future actions to be taken.

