**Table 1. Reasons for withdrawal or referral.**

| Reasons for withdrawal                                                        | Further nutritional supplement         | Further follow-up                                                                   | Further assessment                                                                                                             |
|---------------------------------------------------------------------------------------------------------|------------------------------------------------------|---------------------------------------------------------------------------------------------------|----------------------------------------------------------------------------------------------------------------------------------------------|
| Withdrawals                                                                               |                                                      |                                                                                                   |                                                                                                                                              |
| Spontaneous withdrawal of consent                                                                       | None                                                 | None                                                                                              | None                                                                                                                                         |
| Defaulters (having missed 2 consecutive visits), visited at home and not keen to come back in the study | None                                                 | Home visit : referral to the ATFC or health center in case the child developed SAM or any illness | - Life and nutritional status at the home visit.
- Reasons for defaulting.                                                                |
| Lost to follow-up (having missed 2 consecutive visits, visited at home but not possible to locate)      | None                                                 | None after unsuccessful home visit                                                                | None                                                                                                                                         |

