| Serious Adverse Events                                                                                  | Local Foods                                          | Until the end of treatment                                                                        | - Outcome of the treatment
- Anthropometric measurements and clinical assessment until end of treatment                                   |
| Other                                                                                     |                                                      |                                                                                                   |                                                                                                                                              |
| Transfer to the ATFC or ITFC,                                                                           | RUTF or food as provided at the ITFC or the hospital | Until the end of treatment                                                                        | - Outcome of the treatment
- Anthropometric measurements and clinical assessment until end of treatment                                   |
| Hospitalization                                                                                         | Continue intervention                                | Until the end of treatment                                                                        | - Medical follow-up
Outcome of the treatment
- Anthropometric measurements and clinical assessment until end of treatment  |

 Participants who withdraw informed consent or were lost to follow-up will not receive further incentives. Other participants will receive the incentives according to the planned timing at the start of the study.

 Children receiving other nutritional intervention (which is not part of Study) after being referred, they will be considered as failure to respond to treatment, and data obtained after receiving other nutritional intervention than previewed will not be included for data analysis

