### *3.1.7. Sample size*

In the absence of information on the increase of LBM from 0-3 months among children with MAM in this age group, we assume that a 0.4 SD difference in change/increase in lean body mass between groups as clinically relevant. The sample size per group,  $n$ , required to detect a change,  $d$ , in a continuous variable with standard deviation,  $s$ , with alpha set at 5% and a 80% power, is  $16*s^2/d^2$ . Hence, to detect a 0.4 SD greater increase in lean body mass between 2 products/cells, we will need 100 children in each group. To allow for a 25% expected loss to follow-up/drop-out in the nutritional program in Burkina Faso, we will include 134 children in each of the 12 intervention groups (cells) then  $12 \times 134 = 1608$  children.

Considering a recruitment rate of 54 children with MAM per month per CSPA, the recruitment is therefore expected to last about 6 months and will be limited five CSPA (i.e., 54 children with MAM \* 6 months \* 5 CSPA = 1620 children).

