## **Questionnaire**

At baseline, socio- demographic and medical characteristics of the participants will be collected using an interviewer-administered baseline questionnaire. At each subsequent fortnightly/monthly visit, caretakers will answer a questionnaire about morbidity. Some questions will also assess the adherence to the food supplement (quantities consumed). In addition, all data on morbidity as collected during the clinical examination by a nurse (symptoms, diagnosis and treatments prescribed) will be recorded in a case-report form. All serious AE will be immediately reported to the study supervisor. Childcare behaviors related to supplementary feeding and adherence to and acceptability of the products will furthermore be explored (as described in the section 3.3). The provisional list of information that will be collected is presented in annex 7. In addition dietary data will also be collected at inclusion, 3 and 6 months.

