### **Safety analysis**

Safety analyses will be performed among participants having been randomized. The number of adverse events and serious adverse events will be presented for each group. Proportion of participants presenting with AE or serious AE will be compared between groups. Description of adverse events will be given.

Statistical analysis will be performed using Stata software.

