## 5. Study schedule and training

. Training of the field team will be ensured by ALIMA and the PhD students of the University of Copenhagen involved in the project. In addition, all partners will ensure regular support. During the study, continuous supervision, regular meetings and reporting will ensure updating of knowledge and permanent training throughout the study.

Recruitment of the children is expected to begin in August 2013 and last for 6 months (Table 3). For each child, the intervention is scheduled for three months, with an additional three months of follow-up of all children participating in the trial. In total, the study is expected to last for one year including follow-up period.

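### No month-6 vital-status check is planned for children who default, are lost, or leave after an SAE or transfer, and the rule for deaths found through defaulting does not mention SAE reporting, so per-group death and SAE counts may be incomplete.

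*Combined protocol and SAP*

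**What the plan says.** Section 5 gives each child three months of intervention "with an additional three months of follow-up of all children participating in the trial". Section 3.1.10 sends a home visit to any child more than a week late for a visit and then states: "Defaulting due to death will be reported with morbidity data".

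Table 1 (section 3.1.6) sets out what happens to children who leave:

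- Withdrawal of consent: no follow-up and no assessment.
- Defaulters who are found but will not return: vital and nutritional status recorded once, at the home visit.
- Children who cannot be located: "None after unsuccessful home visit", and no assessment.
- Children withdrawn for an SAE, or transferred for nutritional treatment: "Anthropometric measurements and clinical assessment until end of treatment".
- Hospitalised children: the same assessments, but the supplement continues.

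Section 3.1.5 lists death as a component of the morbidity outcome. Its Safety footnote makes any event resulting in death an SAE, and the text adds: "All serious AE will be immediately communicated to the trial manager". The Safety analysis part of section 3.1.13 covers all randomised children: "The number of adverse events and serious adverse events will be presented for each group". It then compares the proportions with events between groups. Sections 3.1.3 and Table 1 (footnote 2) drop from analysis any data obtained after a child receives a nutritional intervention from outside the study. Neither states an exception for deaths or SAEs.

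**The concern.** The safety comparison uses all randomised children, but the follow-up rules do not supply all of their deaths. For a child who has defaulted, cannot be found, or has finished treatment after an SAE or transfer, a later death has no planned route into the data. For a child whose death is discovered at a home visit, the sentence that governs recording names the morbidity data and not the SAE route. Site staff could therefore record it in one place only.

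The stake is a biased comparison as well as a low total. Section 3.1.14 accepts that withdrawal and loss may depend on the allocated group. Section 3.1.9 says families know whether they have LNS or iCSB, so different default rates between those arms are plausible. If one arm loses more children, fewer of its deaths are seen and it can look safer than it is. Children who default or are transferred may also be at higher risk of death than those who stay.

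**Working it through.** **The plan's own figure.** Section 3.1.7 gives the sample size per group, "with alpha set at 5% and a 80% power, is" 16s²/d². With d = 0.4 SD, 16/0.16 = 100 evaluable children. Allowing for 25% loss, 100/0.75 = 133.3, rounded up to 134 per product, and 12 × 134 = 1608. These figures reproduce. The allowance corresponds to 0.25 × 1608 = 402 children, or 33.5 per product.

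**Illustrative mortality (assumption).** The only mortality figure in the documents is in section 1.4: 176 deaths per 1000 live births before age 5, nationally. Spread evenly over 60 months, the six-month risk is 1 − (1 − 0.176)^(6/60) = 1.92%. That is 0.0192 × 1608 ≈ 30.8 deaths, or about 2.6 per product. It is not specific to children of 6-23 months with MAM.

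**Share of deaths unseen, average risk after leaving.** The unseen share is the loss proportion times the fraction of six-month risk that falls after the child leaves.

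| When children leave | Fraction of risk after leaving | Unseen, 25% loss | Unseen, 10% loss | Deaths seen of 30.8 (25% loss) |
|---|---|---|---|---|
| Month 0 | 1 | 25% | 10% | 23.1 |
| Evenly over months 0-3 | about 0.75 | 18.7% | 7.5% | 25.1 |
| Month 3 | about 0.5 | about 12.5% | 5% | 27.0 |

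The percentages hardly depend on the mortality assumed; the counts do. At 0.5% risk, 6.0 to 7.0 of 8.0 deaths would be seen. At 3%, 36.2 to 42.3 of 48.2 would be seen.

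**Higher risk after leaving (25% loss).** Let f be the fraction of risk before leaving and R the risk ratio afterwards. The unseen share is 0.25(1 − f)R / [0.75 + 0.25(f + (1 − f)R)].

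- R = 2: month 0 gives 0.50/1.25 = 40%; month 3 gives 0.25/1.125 = 22%.
- R = 3: month 0 gives 0.75/1.50 = 50%; month 3 gives 0.375/1.25 = 30%.

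**Unequal loss (assumed 15% v 35%, equal true risk of 1.92%).**

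- Loss at month 0: 85% v 65% of deaths are seen, an apparent ratio of 0.65/0.85 = 0.76. Per product, 2.2 v 1.7 deaths. For two arms of six products (804 children each), 13.1 v 10.0.
- Loss spread over months 0-3: 89% v 74% are seen, a ratio of 0.83. Per product, 2.3 v 1.9. Per arm, 13.7 v 11.4.

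Treating the counts as Poisson, 2.2 v 1.7 is a difference of 0.5 with a standard deviation of √(2.2 + 1.7) ≈ 2.0. The arm-level difference of 3.1 has a standard deviation of √(13.1 + 10.0) ≈ 4.8. Neither would stand out from chance. The distortion is systematic, but small beside the sampling noise.

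**The case against.** Much can be said for the plan, and several stronger readings fail.

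A reader might infer that deaths are not sought in a quarter of the children. The documents do not support that. Every child more than a week late is to be visited at home, so a child who dies while enrolled triggers a search. The 25% is a planning allowance that sizes 100 evaluable children for the three-month lean-mass outcome. Only deaths after a child has left, or in children who cannot be found, are exposed.

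A reader might also infer that recording a death with morbidity removes it from the SAE count. It need not. Death is a component of the morbidity outcome, the regular-visit questionnaire collects morbidity and adverse events together, and the duty to report SAEs at once has no exception for deaths at home. What stands is that the two rules are not joined, and the section that handles missing children mentions only one of them.

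The hospitalisation row continues the supplement and is not listed as a withdrawal, so those children may well keep their regular visits to month 6. The follow-up promise in section 5 concerns children participating in the trial, and a child who has left for good is arguably outside it. Section 3.1.14 also promises defaulter tracing in all arms, though it gives no time point and no vital-status item.

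Finally, "All serious AE will be immediately communicated to the trial manager" and "All serious AE will be immediately reported to the study supervisor" name different recipients. A reader might see a conflict, but both require immediate reporting and the roles may coincide. That is a clerical matter and does not affect the counts.

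None of this supplies the month-6 check.

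**Conclusion.** The gap is real but limited. Table 1 states when observation ends, and for defaulters, children who cannot be located, SAE withdrawals and transfers it can end before month 6 with no later check on survival. The rule for deaths found through defaulting does not point to the SAE route. The comparison of deaths and SAEs among all randomised children may therefore be incomplete, and unequal if loss differs by group. The documents do not show that counts will be too low.

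Under the 25% allowance and average risk after leaving, roughly 12% to 25% of six-month deaths would be unseen. With two or three times the risk the range is 22% to 50%, and with 10% loss and average risk it is 5% to 10%. These ranges rest on assumed timing and risk after leaving; the numbers of deaths also rest on an assumed mortality. Mortality is not the primary outcome, and no single-product comparison would turn on this. It is worth correcting because death is the most serious event the trial records and the correction is cheap.

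**What to change.** 1. Section 3.1.10: state that every death, including one learned of at a home visit or after default or transfer, is also recorded and reported as an SAE and counted in the safety analysis. It can still be shown with morbidity.
2. Table 1: in every row except withdrawal of consent, add vital status at month 6, with its date. Obtain it at the clinic or through the two community health workers that section 1.4 places in each village.
3. Section 3.1.13, Safety analysis: report deaths by assigned product for all randomised children, with the number of unknown vital status beside them.
4. Reconcile the exclusion of data after other nutritional intervention (section 3.1.3 and Table 1, footnote 2) with the all-randomised safety set, so that deaths and SAEs are not dropped.

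The cost is some wording in the protocol and case-report form, plus one alive/dead query for each child who left without withdrawing consent. That is at most about 402 queries if loss reaches the planning allowance. Some children will remain unlocatable, which is why the unknowns should be shown. The reported death count may rise. No treatment rule changes.

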**Table 2. Follow-up chart of the participants.**

| Time (months)                                                                                                                                                    | 0       | 1 | 2 | 3 | 4 | 5 | 6 |
|------------------------------------------------------------------------------------------------------------------------------------------------------------------|---------|---|---|---|---|---|---|
| Fortnightly visits                                                                                                                                               | X       | X | X | X | X | X | X |
| Screening for eligibility                                                                                                                                        | ○       |   |   |   |   |   |   |
| Recruitment/consent/randomization                                                                                                                                | ○       |   |   |   |   |   |   |
| Baseline questionnaire (socio-demographic and medical characteristics)                                                                                           | ○       |   |   |   |   |   |   |
| Food supplementation (LNS & iCSBs arms)                                                                                                                          | ←-----→ |   |   |   |   |   |   |
| Education on nutrition, hygiene and health                                                                                                                       | ○       | ○ | ○ | ○ |   |   |   |
| Regular visits ( Questionnaire including morbidity and possible adverse events, clinical examination by a nurse and adherence questionnaire ) | ○       | ○ | ○ | ○ | ○ | ○ | ○ |
| Anthropometry: weight, MUAC, knemometry and triceps- and subscapular skinfold                                                                             | ○       | ○ | ○ | ○ | ○ | ○ | ○ |
| Anthropometry: height, crown-rump length                                                                                                                  | ○       | ○ | ○ | ○ | ○ | ○ | ○ |
| Blood sampling (Hemoglobin, malaria, serum AGP, CRP, IGF-1, micronutrient status, essential fatty acids)                                                  | ●       |   |   | ● |   |   | ● |
| Lean Body Mass (deuterium dilution test)                                                                                                                         | ○       |   |   | ○ |   |   |   |
| Physical activity                                                                                                                                                | ○       |   |   | ○ |   |   | ○ |
| Child development (milestones)                                                                                                                                   | ○       |   |   | ○ |   |   | ○ |
| Acceptability questionnaire                                                                                                                                      |         | ○ |   | ○ |   |   |   |
| Dietary questionnaire                                                                                                                                            |         | ○ |   | ○ |   |   | ○ |
| Thymic size (Ultrasound)                                                                                                                                         | ○       |   |   | ○ |   |   | ○ |

 Including malaria rapid test and hemoglobin measurement using the hemocue if necessary.

